### 5.3 Outcome Measures

#### 5.3.1 Definitions of Terms

- **Caseous necrotic nodule:** closed lesion generally encapsulated with fibrotic tissue, and containing a caseous necrotic center surrounded with multiple cellular layers
- **Cavity:** thick-walled open lesion communicating with an airway and often containing liquefied necrotic material
- **Permeability coefficient (P):** the speed at which a compound moves through a tissue, generally due to diffusion but also to facilitated transport. Its units are cm/sec. In this study, the parameter to be determined for the rate of penetration of a drug to the lesions will be a combination permeability-surface area (PS) coefficient.
- **Penetration ratio:** the ratio between the area under the concentration-time curve in lesion and in blood or  $AUC_{\text{lesion}} : AUC_{\text{plasma}}$  [51].

#### 5.3.2 Primary Endpoint

The comparison between the relative permeability coefficients of RIF and KM in pathologically defined large caseous necrotic nodules. The relative permeability coefficient is estimated from the pooled PK data as the ratio of the permeability in diseased tissue over that in healthy tissue.

#### 5.3.3 Secondary Endpoints

- 1) The comparison between the absolute permeability coefficients of each of the five drugs in uninvolved lung and in closed necrotic lesions
- 2) The comparison between the relative permeability coefficients of RIF, KM, INH, PZA and MXF in caseous necrotic nodules versus open cavities

- 3) The comparison between the exposure ratio or ratio between the Area Under the Curve ( $AUC_{0-24}$ ) in lesions ( $AUC_{\text{lesion}}$ ), uninvolved lung ( $AUC_{\text{lung}}$ ) and plasma ( $AUC_{\text{plasma}}$ ) for RIF and KM in large caseous necrotic nodules
- 4) The comparison between the exposure ratio or ratio between the Area Under the Curve ( $AUC_{0-24}$ ) in plasma ( $AUC_{\text{plasma}}$ ), uninvolved lung ( $AUC_{\text{lung}}$ ) and lesions ( $AUC_{\text{lesion}}$ ) for each drug in each lesion type
- 5) Standard PK/PD indices for each drug in each lesion type ( $AUC_{0-24}/MIC$ ;  $AUC_{0-24}/MBC$ ;  $AUC_{0-24}/MPC$ ;  $C_{\text{avg}}/MBC$ )
- 6) The correlation between permeability coefficients of the 5 study drugs and lesion type, determined by histopathology and HRCT
- 7) The correlation between permeability coefficients of the 5 study drugs and their respective physico-chemical properties
- 8) The correlation between macroscopic observations from High-Resolution CT and Dynamic MRI with lesion types as determined by microscopic histopathological observations
- 9) The concentration gradients of the five study drugs within the different layers of closed lesions, as determined by mass spectrometry imaging across tissue sections
- 10) The distribution and function of the vascular network present around individual lesions, determined by analyzing dynamic MRI values

## 5.4 Statistical Methods for Data Analysis

### 5.4.1 Primary Analysis

Descriptive statistics will be calculated to assess subject characteristics as a whole, as well as by the drug-delivery group assignment. Statistical summaries will also be calculated for the measured drug physico-chemical properties and in vitro PK parameters. These statistics include: for categorical variables, the number and percent in each category; for continuous variables, the mean, median, standard deviation, and range (minimum, maximum).

The primary analysis of the primary endpoint will use the parameter and variance estimates from the population PK model for the relative permeability (P) of disease tissue (large necrotic nodules) compared to healthy tissue for KM and RIF. From the model estimates, a 95% confidence interval for the difference in the relative P for RIF and KM will be calculated. If 0 lies outside the 95% confidence interval, the difference in permeability for the 2 drugs is declared significant.

An analysis of the primary endpoint will take place once the final subject has completed his/her surgery and all samples have been analyzed.

### 5.4.2 Secondary Analysis

A brief description of some of the planned analysis for secondary endpoints is given below. In a manner similar to the primary analysis, pair wise comparisons of relative permeability between other pairs of drugs for a fixed tissue type, as well as the relative permeability comparison for caseous necrotic nodules versus open cavities for each drug, will be examined by calculating the 95% confidence intervals for the difference estimated from the model parameters and variance

for each comparison of interest. Confidence intervals for examining the difference in exposure ratios between the AUC in plasma, uninvolved lung, and lesions for each drug and lesion type will be generated using Monte Carlo simulation and the model estimates for the relevant parameter and their variances. A similar analysis will also be done for the other standard PK/PD indices of interest.

The correlation between the permeability coefficients and physico-chemical properties for the 5 study drugs will be examined graphically by plotting the values of the permeability against different measured physico-chemical properties for each of the study drugs and lesion types.

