### 2.2 Secondary Objectives

- 1) To determine the absolute penetration efficiency of each of the five drugs in uninvolved lung tissue and in closed necrotic lesions and cavities
- 2) To compare the penetration of RIF, INH, PZA, MXF and KM into closed caseous necrotic lesions versus open cavities
- 3) To compare the levels of RIF and KM in plasma versus caseous necrotic lesions over time
- 4) To compare the levels and exposure of all study drugs in plasma, normal lung and lesions

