## 5 An Analysis of the Study---Statistical Methods and Justification

### 5.1 Definition of Terms and PK Parameters Used in Primary and Secondary Endpoints, and in Statistical Analysis

In this study, the primary endpoint will be the relative **permeability coefficient** (*P*) of the two primary study drugs, rifampicin (RIF) and kanamycin (KM) in large necrotic nodules.

Permeability coefficient (*P*): the speed at which a compound moves through a tissue, generally due to diffusion but also to facilitated transport. Its units are cm/sec. In this study, the parameter to be determined for the rate of penetration of a drug to the lesions will be a combination permeability-surface area (**PS**) coefficient. This combined parameter is a flow, its units are cm^2.cm/sec or volume/time, but it can also be thought of as a diffusion-length term (cm^2s.cm).

Relative permeability coefficient: the ratio of the permeability coefficient for diseased tissue over that for healthy tissue. Due to the limited tissue samples that will be available for estimating permeability, we will pool the tissue data for all subjects within a single drug group to determine the relative permeability of drug to diseased nodules versus healthy lung tissue. This will allow us to work with all the tissue samples for a given subject group to simultaneously model the permeability data. By assessing its relative value to healthy tissue, it decreases the dimensionality of the model and thus will help to obtain better estimates with limited data.

Diffusion rate constant: the constant which links the change of drug concentration over time to the concentration gradient according to the following equation:

$$dC_{\text{lesion}}(t)/dt = k_{12} \cdot [C_{\text{plasma}}(t) - C_{\text{lesion}}(t)] - k_{21} \cdot [C_{\text{lesion}}(t) - C_{\text{plasma}}(t)]$$

***k*12**: diffusion rate constant from blood (compartment 1) to lesion (compartment 2);

***k*21**: diffusion rate constant from lesion to blood.

The diffusion rate constant is a function of the permeability coefficient:

$$k_{12} = PS/V_1 \quad k_{21} = PS/V_2$$

where *V*1 and *V*2 are the volumes of the two interconnected compartments (to be estimated from the drug concentration profiles in plasma and lesions).

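### The within-drug nodule-versus-cavity comparison is set on permeability relative to lung, so uncertainty in lung permeability enters a contrast from which it could cancel

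*Protocol*

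**What the plan says.** Secondary objective 2 (protocol 2.2) is "To compare the penetration of RIF, INH, PZA, MXF and KM into closed caseous necrotic lesions versus open cavities". It makes no reference to healthy lung.

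Secondary endpoint 2 (5.3.3) turns this into "The comparison between the relative permeability coefficients of RIF, KM, INH, PZA and MXF in caseous necrotic nodules versus open cavities". Section 5.1 defines the relative coefficient as "the ratio of the permeability coefficient for diseased tissue over that for healthy tissue" and adds that "we will pool the tissue data for all subjects within a single drug group", so each drug has one healthy-lung P that serves as divisor for every lesion type. The reason given for the relative scale is that it "decreases the dimensionality of the model and thus will help to obtain better estimates with limited data".

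Section 5.4.2 fixes the method: "the relative permeability comparison for caseous necrotic nodules versus open cavities for each drug, will be examined by calculating the 95% confidence intervals". It follows the pattern of the primary analysis and uses "confidence intervals for the difference estimated from the model parameters and variance". The primary rule in 5.4.1 is: "If 0 lies outside the 95% confidence interval, the difference in permeability for the 2 drugs is declared significant".

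**The concern.** The question is nodule against cavity within one drug. The stated contrast divides both sides by the same estimated lung P and then takes a difference. The hypothesis of equal lesion permeability does not involve lung P, but the interval for the difference does. If lung P is estimated imprecisely, the interval widens in proportion to the difference itself, and a real contrast between lesion types can be masked by something unrelated to either lesion.

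At stake is the reading of five within-drug comparisons. An interval that includes 0 could reflect poor knowledge of lung P rather than similar penetration into closed and open lesions.

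**Working it through.** **The plan's own figure.** No precision or power is stated for this comparison. The 50% variability used below comes from the sample-size section (5.2), whose figure reproduces. Means 1 and 0.5, SDs 0.5 and 0.25 and correlation 0 give an SD of the difference of √(0.25 + 0.0625) = 0.559 and a standardised difference of 0.894. A two-sided 5% paired t-test then needs 12 subjects (power 80.5%), and 12/0.8 = 15.

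**Step 1, the contrast.** P_nodule/P_lung − P_cavity/P_lung = (P_nodule − P_cavity)/P_lung = D/P_lung.

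**Step 2, its variance.** By the delta method, with lung error independent of lesion error:

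Var(D/P_lung) ≈ [Var(D) + D² × RSE²]/P_lung²

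Hence 1/z²(planned) = 1/z²(direct) + RSE², where RSE is that of lung P. So z(planned) cannot exceed 1/RSE, and above RSE = 1/1.96 = 51% it cannot reach 1.96. Equivalently, the planned interval excludes 0 only if the direct z exceeds 1/√(1/1.96² − RSE²), rather than 1.96.

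**Step 3, numbers for n = 12.** Each lesion P is given an RSE of 50%/√12 = 14.4%. This counts only the stated variability and is therefore optimistic. For a two-fold difference, z(direct) = 0.5/√(0.3125/12) = 3.10.

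| RSE of lung P (assumed) | z, two-fold | z, 100-fold | direct z needed |
|---|---|---|---|
| 0 | 3.10 | 6.86 | 1.96 |
| 14.4% | 2.83 | 4.87 | 2.04 |
| 30% | 2.27 | 3.00 | 2.42 |
| 40% | 1.95 | 2.35 | 3.16 |
| 50% | 1.68 | 1.92 | 9.85 |
| 60% | 1.47 | 1.62 | none suffices |

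Expected z for a two-fold difference drops below 1.96 at RSE = √(1/1.96² − 1/3.10²) = 40% for n = 12. With n = 15 (direct z 3.46) this happens at 42%.

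**Step 4, simulation.** 200,000 draws were made with log-normal errors, lesion RSE 50%/√15 = 12.9% and a two-fold difference. Comparing the lesions directly gave power of about 96% whatever the lung RSE (absolute difference 96.3%, log ratio 96.7%). The planned contrast gave 95.7% at lung RSE 12.9%, 89.8% at 30%, 65.3% at 40% and 0% at 50% or more.

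**Step 5, could lung P be that imprecise?** The documents do not say, so this is illustration only. Assume uptake of 0.1/h (nodule), 0.3/h (cavity) and 2/h (lung), a plasma half-life of 3 h, 30% residual error and 50% variability in P. The standard errors of ln P are then 0.17, 0.18 and 0.61:
- Lesion variance: 0.017² + 0.054² = 0.0032.
- Lung term: 0.2² × 0.61² = 0.0149.
- z = 0.2/√0.0032 = 3.5 directly, and 0.2/√0.0181 = 1.5 on the planned scale.

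The result depends on the inputs. Residual error of 20–47% and half-life of 2–4 h put the lung RSE at 0.31–1.10. Averaging three lung samples per subject gives about 0.38–0.41, and lung uptake of 1/h gives about 0.31–0.33. In the same example, a lung RSE of 14.4% gives z = 3.15 and one of 31% gives z = 2.4. It falls below 1.96 only above about 42%.

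**Step 6, the log ratio.** log(P_nodule/P_lung) − log(P_cavity/P_lung) = log(P_nodule/P_cavity). Lung P cancels exactly. For the two-fold case at n = 12, z = 0.693/√(2 × 0.25/12) = 3.40 at any lung RSE.

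**The case against.** Four points on the other side have weight.

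- **The loss is conditional on an unstated figure.** A reader might infer that the comparison is bound to show nothing. The documents do not support that. The only variability they give is 50%, which at n = 12 is an RSE of 14.4% and costs little, and the dissection plan in 3.4.2 calls for more than one sample of normal-looking lung. On the other side, 14.4% ignores residual error and each subject gives tissue at only one time, so larger values cannot be excluded.
- **The cap needs a symmetric natural-scale interval and independent errors.** A percentile interval simulated from the model excludes 0 exactly when the interval for P_nodule − P_cavity does, because lung P is positive. If the lung error has positive correlation r with the error of the lesion difference, the cap rises to 1/(RSE × √(1 − r²)). Both points stand. However, 5.4.2 mentions Monte Carlo simulation for exposure ratios and the PK/PD indices, not for permeability, where it names a difference built from estimates and variances.
- **Lesion types are examined elsewhere without the lung divisor.** Endpoint 6 relates permeability coefficients to lesion type, so it would be wrong to infer that no endpoint does so. But it is framed as a correlation, endpoint 1 does not name cavities, and endpoint 4 concerns exposure. None of them is a direct nodule-to-cavity contrast of P.
- **The relative scale is a reasoned choice.** The argument in 5.1 concerns fitting a model to sparse data. It can stand as the parameterisation without requiring a within-drug lesion contrast to be a difference of ratios. A plain difference of absolute P is not clearly better, since it can carry error shared by all tissues of a subject. The log ratio removes a common proportional error as well as lung P.

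**Conclusion.** The point holds in a conditional form. The protocol fixes a contrast that brings lung uncertainty into a question that is not about lung. Under a symmetric interval and independent lung error, z is bounded by 1/RSE of lung P. The loss is small at an RSE of about 14%, takes a two-fold difference below expected significance at about 40%, and is total above 51%. Which of these applies cannot be told from the documents.

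A reader might also infer that relative P is the wrong scale throughout, or that the primary result is at risk. Neither follows. The primary comparison is between RIF and KM, each with its own lung P, so nothing cancels there and lung is part of the stated objective. The sample size rests on a different calculation and is untouched. This is an improvement to one secondary endpoint.

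**What to change.** In secondary endpoint 2 and section 5.4.2, state that for each drug the nodule-versus-cavity comparison is log(P_nodule/P_cavity), equivalently the log ratio of the two relative P values, with a 95% CI from the model covariance matrix, back-transformed to a ratio. If the model is parameterised in relative P, the covariance between the two relative parameters must be used, because that is where the shared lung error sits. Keep relative P as the parameterisation and for comparisons between drugs.

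The cost is one sentence. The data and the model are the same, and no further subjects or samples are needed.

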## 6 Adverse Event Reporting Plan

### 6.1 Definition of an Adverse Event

*Adverse Events* (AEs) are any unfavorable and unintended diagnosis, symptom, sign (including an abnormal laboratory finding), syndrome or disease which either occurs during the study, having been absent at baseline, or, if present at baseline, appears to worsen. Stable chronic conditions which are present prior to clinical trial entry and do not worsen are not considered AEs and will be accounted for in the subject's medical history.

*Serious Adverse Events* (SAEs) are any untoward medical occurrences that: (1) result in death, (2) are life-threatening, (3) require (or prolong) hospitalization, (4) cause persistent or significant disability/incapacity, (5) result in congenital anomalies or birth defects, or (6) are other conditions which in the judgment of the investigators represent significant hazards.

*Expected Adverse Events* are AEs that are listed as possibly related to the study agent/intervention in the protocol, informed consent document, or the package insert.

*Unanticipated problem that is not an Adverse Event (UPnonAE)*: An unanticipated problem that does not fit the definition of an adverse event, but which may, in the opinion of the investigator, involves risk to the subject, affect others in the research study, or significantly impact the integrity of research data. For example, report occurrences of breaches of confidentiality, accidental destruction of study records, or unaccounted-for study drug.

*Protocol Violation*: Any change, divergence, or departure from the study procedures in an IRB-approved research protocol that has a major impact on the subject's rights, safety, or well-being and/or the completeness, accuracy or reliability of the study data.

*Protocol Deviation*: Any change, divergence, or departure from the study design or procedures of a research protocol that is under the investigator's control and that has not been approved by the IRB. It does not have a major impact on the subject's rights, safety or well-being, or the completeness, accuracy and reliability of the study data.

*Unanticipated Problem (UP)* is any incident, experience, or outcome that is:

1. unexpected in terms of nature, severity, or frequency in relation to
  - a. the research risks that are described in the IRB-approved research protocol and informed consent document; Investigator's Brochure or other study documents; and
  - b. the characteristics of the subject population being studied; and

2. related or possibly related to participation in the research; and
3. places subjects or others at a greater risk of harm (including physical, psychological, economic, or social harm) than was previously known or recognized.

## 6.2 Grading Adverse Events for Severity

The severity of each AE will be determined using the modified DAIDS Table for Grading Adult Adverse Experiences. This table can be found using the following link: [DAIDS 2004 Toxicity Table](#). Any events that are not listed in this toxicity table will be graded by the local PI as follows:

|                            |                                                                                                                                                              |
|----------------------------|--------------------------------------------------------------------------------------------------------------------------------------------------------------|
| Grade 1 - Mild             | Transient or mild discomfort; no limitation in activity; no medical intervention/ therapy required                                                           |
| Grade 2 - Moderate         | Moderate limitation in activity – some assistance may be needed; no or minimal medical intervention/ therapy required                                        |
| Grade 3 - Severe           | Marked limitation in activity; some assistance usually required; medical intervention/therapy required, hospitalizations possible                            |
| Grade 4 - Life-threatening | Extreme limitation in activity, significant assistance required; significant medical intervention/therapy required, hospitalization or hospice care probable |
| Grade 5 - Death            |                                                                                                                                                              |

## 6.3 Assessing Adverse Events for Relationship to Study

Any AE that occurs in a subject will be assessed for its relationship to the study. A causal relationship means a drug caused (or is reasonably likely to have caused) the AE. This usually implies a relationship in time between one or more drugs/study agents and the AE—for example, the AE occurred shortly after the subject received the drugs/study agents.

For all AEs, the clinician who examines and evaluates the subject will determine the AE's causality based upon the temporal relationship to administration of the study agents, the pharmacology of the study agents, and his/her clinical judgment.

The following scale will be used to reflect the PI's judgment as to the relationship between the study agents and the AE:

***Definitely Related:*** The AE is clearly related to one or more of the study agents – follows a reasonable temporal sequence from administration of one or more of the study agents, follows a known or expected response pattern to the one or more of the study agents that is confirmed by

improvement on stopping and reappearance of the event in repeated exposure and that could not be reasonably explained by the known characteristics of the subject's clinical state.

***Probably Related:*** The AE and administration of the study agents are reasonably related in time and/or follows a known pattern of response, and the AE is more likely explained by one or more of the study agents than other causes.

***Possibly Related:*** AE follows a reasonable temporal sequence from administration of the study drugs, follows a known or expected response pattern to the suspected drug or drugs, but that could readily have been produced by a number of other factors.

***Unlikely Related:*** A potential relationship between one or more of the study agents and the AE could exist (i.e., the possibility cannot be excluded), but the AE is most likely explained by causes other than one or more of the study agents (e.g., could readily have been produced by the subject's clinical state or could have been due to environmental or other interventions)

***Unrelated:*** AE is clearly not related to one or more of the study agents – another cause of the event is most plausible and/or a clinically plausible, temporal sequence is consistent with the onset of the event and the study medication administration and/or event is biologically implausible.

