### 3 Study Design and Methods

#### 3.1 Design

This is a single-dose pharmacokinetic study of 5 concomitant drugs where resected lung tissue will be recovered to determine and compare drug levels within plasma, sputum, healthy lung and pulmonary TB lesions over a 24h period. Comparison and modeling of the concentration-time profiles in plasma and lesions are used to infer permeability coefficients, exposure ratios and concentration gradients for five major 1st and 2nd line TB drugs: RIF, INH, PZA, KM and MXF. Subjects will be randomized to receive the 5 drugs at one time point, either at 2, 4, 8, 12 or 24h prior to surgery, or as close as practical to those times with careful recording of the time of administration. Enrollment will continue until evaluable tissues from 3 subjects have been processed at each assigned time point. Blood and sputum samples will be obtained just before drug administration (trough), and blood samples will also be obtained at 2h ( $C_{max}$ ) and 6h post-dosing or as practicable. Whenever possible, one additional blood and/or sputum sample will be obtained between drug dosing and surgery. Finally, blood will be collected at the time of central line placement and sputum at the time of intubation prior to surgery. The time of each blood draw and sputum collection will be recorded as carefully and accurately as possible. Urine will be systematically collected between the time of drug administration and surgery. The removed tissue will be dissected to separate lesion material from uninvolved lung. The location of each lesion within the lung lobes will be recorded. Each lesion will be measured and weighed, then further divided to perform the following analyses: determination of overall lesional drug concentrations by liquid chromatography-mass spectrometry (LCMS), imaging mass spectrometry and histopathology analyses to visualize 2D drug distribution within lesions. A pre-operative dynamic MRI scan (30-60 min duration) will be conducted one to two weeks prior to surgery to assess lesional perfusion and endothelial function. This procedure can be performed with most MRI machines in clinical use and this may be taken at a different site. A scan will be obtained before injection of the contrast agent (gadolinium). After the contrast agent is given, the subject will be scanned serially at several time points up to 8 minutes post-injection. The rate of gadolinium uptake and its retention properties will be determined using software. The entire scan will take about 45 minutes. A subject will participate in this study from entry (1 to 2 weeks prior to surgery), through surgery and for 48h post surgery.

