## **7.7 Study Sites AE Reporting**

Since the subjects on this protocol will be seen because of illness, and are likely to be ill at baseline, many will have AEs by the above criteria. However, their medical management will be standard of care for those illnesses and complications and not part of the research process. Therefore, AEs associated with the underlying disease will not be recorded as AEs. However, AEs assessed to be related to the research will be recorded as such. As described below, all SAEs will be recorded and reported.

Any grade 3 or 4 AE (as defined in Section 7.1) that is possibly, probably or definitely related to study drugs and occurs between the times a subject signs the informed consent form and the time s/he completes the planned surgery (or at the time of early discontinuation of the subject from study participation for any reason) will be captured and recorded and reported with continuing annual review.

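### The causality scale in 6.3 does not fit the reporting rules it feeds: 'possibly related' demands a known reaction pattern, and only the study drugs are rated

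*Protocol*

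**What the plan says.** Section 6.3 opens by promising to assess each AE for its relationship to the study. It then narrows the question: "A causal relationship means a drug caused (or is reasonably likely to have caused) the AE". The five rating levels refer to study agents or study drugs, and the section headed Study Agents describes only RIF, INH, PZA, KM and MXF.

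Three levels matter here:
- 'Possibly related' needs plausible timing, needs that the event "follows a known or expected response pattern to the suspected drug or drugs", and allows that other factors could readily have produced it.
- 'Probably related' needs the event and dosing to be "reasonably related in time and/or follows a known pattern of response", with the drug the likelier explanation.
- 'Unlikely related' keeps a link conceivable, "but the AE is most likely explained by causes other than one or more of the study agents".

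The ratings feed rules with a different scope. In 6.1 an unanticipated problem is "unexpected in terms of nature, severity, or frequency in relation to" the described risks and the study population, and also "related or possibly related to participation in the research". Sections 7.8 and 7.9.1.1 send SAEs at least possibly related to the research to the NIAID IRB within 7 days, expected or not. Section 6.4 has the CRF record relationship to the agent or intervention. The grade 3/4 rule in 7.7 is narrower and captures an event "that is possibly, probably or definitely related to study drugs".

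On imaging, 3.1 states: "A pre-operative dynamic MRI scan (30-60 min duration) will be conducted one to two weeks prior to surgery". Gadolinium is injected during that scan, and willingness to receive it is an inclusion criterion (4.2.1).

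**The concern.** Expedited safety reporting exists largely to find reactions nobody has described before. A scale that makes a known pattern a condition of 'possibly related' works against that purpose, and here the stricter test sits on the lower level of the scale. Patients with tuberculosis who are about to have lung surgery will often have another plausible explanation for an event, so 'possibly' is the level a new reaction would usually need.

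The second mismatch is scope. The study adds a contrast-enhanced scan as well as five drugs, but the only scale supplied asks about drugs. Where a rule depends on the rating, a reaction to the scan has no proper place on it.

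What is at stake is how quickly, and by which route, a small set of events reaches the NIAID IRB. The primary endpoint is not affected.

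**Working it through.** No arithmetic applies. The check sets the wording of the scale against each rule that uses it.

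**Step 1: rate a drug reaction of a previously unknown kind, plausibly timed, with a competing cause.**
- 'Possibly': not met, because there is no known or expected pattern.
- 'Probably': met only if the drug is the likelier cause, since timing alone can satisfy the first limb.
- 'Unlikely': strictly needs another cause to be the most likely one.

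If the drug and the other cause are about equally credible, no level fits. Both 'possibly' and 'unlikely' speak of events that other factors could readily produce, so the known-pattern condition is the main wording that separates them. Its absence pushes the rating down. The event can therefore be rated below 'possibly', although the text does not force this.

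**Step 2: rate a gadolinium reaction.** Section 3.1 puts the scan one to two weeks before surgery, and 3.3.2 puts it within 14 days. The study dose is given 2 to 24 hours before surgery (3.3). A contrast reaction would therefore normally precede the study dose. The scale has no category for a study procedure, and 'unlikely' names other interventions as an alternative cause.

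**Step 3: apply each rule.**

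| Rule | Causality test | Unknown-kind drug reaction rated below 'possibly' | Gadolinium reaction |
|---|---|---|---|
| 7.7, SAE recording | none | caught if serious | caught if serious |
| 7.7, general AE recording | related to the research | depends on the rating | covered in words, but no scale for it |
| 7.7, grade 3/4 capture | at least possibly related to study drugs | missed | missed |
| 7.8 and 7.9.1.1, related SAEs, 7 days | at least possibly related to the research | missed | covered in words, but no scale for it |
| 7.9.1.1, deaths, 7 days | none | caught | caught |
| 7.9.1.1, unanticipated problems, 7 days | own test in 6.1 | caught if judged possibly related and a greater risk | caught if unexpected and a greater risk |
| 7.9.2, death or life-threatening SAE to RCHSPB Safety, 7 days | none | caught | caught |
| 7.9.3 and 7.9.4, SAEs at Asan and PNUH | none | caught if serious | caught if serious |
| 7.9.5, NMC | related to design, intervention or agent | depends on the rating | intervention is named |

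**Step 4: what the rating changes.** For a non-fatal SAE, a rating below 'possibly' moves it from the 7-day related-SAE route to the summary of unrelated SAEs at continuing review (7.9.1.2, under an annual heading). Accrual is expected to take about 12 months (4.1). If continuing review is yearly, such an event could first reach the NIAID IRB by this route when accrual is nearly over. For a non-serious grade 3 or 4 event, the rating decides whether the specific capture rule applies at all.

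**The case against.** The strongest reply is that the protocol has many overlapping routes, and most do not depend on the scale. All SAEs are recorded and all deaths go to the NIAID IRB in 7 days. Two of the three sites report every SAE occurring there to their own IRB. Deaths and potentially life-threatening SAEs go to RCHSPB Safety whatever the cause. Unanticipated problems have their own relatedness test, framed around taking part in the research. All of this stands, and it limits the point considerably.

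Some stronger readings are tempting but not supported:
- A reader might infer that unexpected reactions and contrast reactions escape capture and reporting altogether. The routes just listed show otherwise.
- A reader might infer that no unexpected event can be rated 'possibly related'. Section 6.1 counts events unexpected in severity or frequency, and these can still follow a known pattern. An event with no known pattern can also be rated 'probably'.
- A reader might infer that every contrast reaction must be scored unrelated. Section 6.3 opens with relationship to the study, the CRF item covers interventions, and some subjects may already be taking a study drug in their regimen.
- A reader might infer that the gadolinium risk was overlooked. Sections 6.6.1 and 10.3.2 list only drug risks, but 4.2.2 excludes gadolinium hypersensitivity and the consent form is not available for this review.

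The reply does not remove the remaining problem. The 7-day related-SAE rule uses the word 'possibly', and 6.3 holds the only definition of it. The grade 3/4 rule is limited to study drugs by its own wording. That rule feeds only the annual review, and research-related AEs are recordable under another sentence of 7.7, so the loss there is modest.

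**Conclusion.** The point holds in a limited form. The scale in 6.3 is narrower than the rules it serves, both in requiring a known pattern for 'possibly related' and in rating drugs only. Two consequences follow:
- A non-fatal SAE of an unknown kind with a competing cause can lose 7-day reporting to the NIAID IRB as a related SAE. The unanticipated-problem, RCHSPB Safety or site routes may still catch it.
- Non-serious grade 3 or 4 events of that kind, or from the gadolinium MRI, fall outside the grade 3/4 capture rule.

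The number of events cannot be estimated, because the protocol gives no rates. The MRI part applies in principle to all of the planned 15 or more subjects.

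The conclusion rests on two assumptions. First, investigators apply the definitions in 6.3 as written; the section also invokes clinical judgment, which could soften the effect. Second, the MRI is a study procedure. That is an inference from its place after consent (3.3.2, 3.4.1), from the inclusion criterion, and from 3.4.3, which names X-rays and CT but not MRI as standard of care. The abstract's sentence on imaging is less clear about this.

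**What to change.** Make three wording changes:
1. In 6.3, define 'possibly related' as a reasonable time sequence, whether or not the event follows a known pattern, where other factors could also readily have produced it. The boundary with 'unlikely' then rests on whether another cause is the most likely one, which 'unlikely' already requires.
2. In 6.3, extend the scale and the sentence defining causality to study agents or study procedures, for example the gadolinium MRI. This matches the CRF item in 6.4.
3. In the grade 3/4 rule in 7.7, replace the reference to study drugs with the research, as in 7.8 and 7.9.1.1.

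The cost is a protocol wording amendment, with CRF instructions brought into line if needed. The downside is that slightly more events will be rated possibly related and reported. In a study of about 15 subjects with a single study dose, that burden should be small.
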